##### Missing data

Despite best efforts, we expect attrition of ~ 10% by 1 month and ~ 15% by 12 months. We will handle missing panel data using direct maximum likelihood (ML) [73–75], which uses all available data provided by a given participant. ML, like multiple imputation, can provide valid inferences when data are “missing at random” and are superior to other methods which are limited to a more stringent assumption of “missing completely at random.”

##### Power analyses

Preliminary to calculations, we conducted a review of the adult and youth CBM anxiety literature to estimate plausible effect sizes. This included the five adult RCTs [18–22], two youth RCTs, [23, 25] and one youth case series [24]. To increase comparability across studies, we calculated within-condition effect sizes (ESs) for anxiety reduction associated with the variants of CBM most relevant for this proposal. For Low-Ratio CBM, we found a mean ES of d = 0.52. For self-administered CBM (often Internet delivered), we found a mean ES of 0.82. Lab-administered CBM yielded a mean ES of 1.39. Finally, CBM with a mix of lab and self-administered sessions yielded a mean ES similar to lab-based studies (mean d = 1.56). From this review we (a) projected the within- and between-condition ES differences we might expect in our proposed design and (b) calculated the effective ES for each of our hypotheses of clinical outcomes. For the comparison of the two High-Ratio CBM conditions vs. Low-Ratio CBM, our review suggests an estimated difference (Δ) ES of d = 0.73. We conservatively powered this analysis for an ES Δ of 0.59, approximately equivalent to an odds ratio of 2.90 [76]. To estimate the ES for the comparison of CBM + AP and High-Ratio CBM, we looked to the literature for estimates of the comparison of lab-administered vs. self-administered CBM. This review suggests an estimated ES Δ of d = 0.57. We chose to power the analysis for this hypothesis with a conservative ES Δ of d = 0.37, which is approximately equivalent to an odds ratio of 1.94 [76].

We conducted power analyses for the primary outcome (via PASS software [77]) to generate the sample required to detect the hypothesized contrasts in a logistic regression model. For our main comparison of the two High-Ratio CBM conditions versus Low-Ratio CBM, with α = .05, we would have 80% power to detect a 20% greater remission (odds ratio = 2.90) in arms 2 + 3 compared to the Low-Ratio arm with 187 participants (n~ 63 per arm) at the 6-month follow-up**.** For the comparison of the two High-Ratio CBM conditions, at an alpha level of .05, we would have 80% power to detect a 16% greater remission (odds ratio = 1.94) in the CBM + AP arm compared to the CBM only arm with 148 participants per arm (*N* = 444 total) at the 6-month follow-up. We based our target sample on the larger N needed to adequately test this latter hypothesis (Arm 2 vs. Arm 3). To compensate for the loss in precision from imputing data for those lost to follow-up, we inflated the target sample size based on an attrition rate of ~ 10% (*N* = 498, or *n* = 166 per arm). This is a conservative adjustment, as the SEs from imputed data results will be less than the SEs from a complete case analysis.

##### Economic analyses

We will conduct incremental cost-effectiveness analyses (CEA) following the methodology recommended by the Panel on Cost-Effectiveness in Health & Medicine [78] and methods used in prior CEAs [79, 80]. For our primary CEA, we will take the health-care organization perspective for 12 months following randomization, calculated from the EQ-5D as the clinical outcome because this allows the broadest comparison to other medical interventions, and is recommended by experts [78]. Although other perspectives, such as the societal perspective, may be important to understand, the healthcare perspective is particularly relevant when the focus is on the healthcare system implementing the intervention. The EQ-5D has been used in numerous previous CEAs, including several with anxiety interventions [81–83]. However, QALYs may not capture all relevant mental health clinical impacts [84–86]. Thus, we will also calculate incremental CEAs using anxiety-free days (AFD) similar to previous anxiety treatment CEAs [81–83, 87–89]. AFDs are one of the most commonly employed outcomes in economic analyses of anxiety treatments [87, 90–93], enabling us to compare our economic results with the rest of the field. As part of the economic evaluation, we will also use instrumental variable methods to attempt to better estimate the effect of CBM dose on QALYs and cost, using potential instruments collected as part of the baseline assessment.

## Discussion

This paper describes the study protocol of a randomized controlled trial (RCT) to assess the benefit of computerized CBM to treat youth with anxiety. This RCT is considered a blended efficacy-effectiveness trial, in that it is highly controlled with detailed, blinded assessments and has a focus on possible treatment mechanisms, but is also conducted in a real-life setting with youth who have sought usual care services for anxiety and who have received a clinical anxiety diagnosis. The primary aim of this study is to assess whether self-administered CBM can be successfully delivered as a self-administered treatment at home, and whether High-Ratio CBM will demonstrate clinical effectiveness. Further, we aim to assess whether High-Ratio CBM with the AP component will result in greater rates of anxiety remission than High-Ratio CBM without AP. Finally, we aim to assess whether self-administered CBM is cost effective to deliver to youth seeking anxiety treatment in a real-world health-care setting.

### Strengths

The study uses a rigorous control condition with a Low-Ratio CBM design, which controls for the effects of time and attention. The youth in all three arms will be asked to complete the same number of sessions over the intervention period, and in each session the youth view the same number of trials. These features bring the rigor of a classic efficacy design and permit confident attributions of outcome effects.

This study will have “effectiveness” elements (such as recruitment via electronic medical records and self-administration of CBM), which will allow us to enroll a sample that is 10 times larger than other published CBM trials. This study will be large enough to have the statistical power to pursue a wide variety of substantive, mechanistic, and economic analyses that smaller lab-based studies could not address. However, the sample will not be so large that we are unable to pursue a detailed evaluation of clinical outcomes.

### Limitations

Although self-administered CBM promises to be an easily disseminated treatment for anxiety, past results have been mixed when CBM has been delivered outside of the lab. It is possible that without any in-person staff support, participants will not adhere to the protocol as closely as if they were in the lab. However, the design of the current study has attempted to address this potential limitation by adding the telephone-based adherence promotion arm to address these potential issues, which will be the first to test the importance of this component. This added component will add additional support provided by research staff to give technical assistance with the use of the program, support/encouragement, motivational enhancement, and brainstorming solutions to barriers. The addition of AP in this trial will attempt to recreate some of the support of in-person lab-based interventions, which we hypothesize will lead to greater clinical effectiveness of the self-administered CBM program.

Another potential limitation is that the control condition is itself an active treatment, albeit of a lower “dose” of negative bias retraining opportunities. While this controls for expectation bias and treatment exposure, it also may prove to be a more a more difficult control condition for the High-Ratio CBM to overcome.

The study is a mixed-blind design, where participants are unaware whether they are being administered the High- or Low-Ratio version of the CBM program. However, with the addition of the AP component in Arm 3, it is impossible for the participants and phone coaches in this arm to be blind to their condition. To address this, we have taken measures to ensure that the research evaluation staff remain blinded to participant condition and complete assessments without knowledge of their assignment, including whether a given participant is receiving AP.

Our planned sample will have approximately 141 participants in each arm at 12-month follow-up, accounting for an expected attrition rate of 10%. A sample this size is sufficient to detect expected clinical differences, but will give us a less than optimal level of power to detect differences in the cost effectiveness analyses which ideally compare hundreds or thousands of cases per condition. Although this is a limitation, the economic evaluation will still provide useful information about the likely effect size related to cost effectiveness for the intervention and this information could help refine the intervention in order to increase its potential for implementation in other health-care settings.

This self-administered CBM intervention overcomes barriers to EBTs for anxiety such as cognitive behavioral therapy and SSRI medication, as well as limitations to previous studies that require participants to attend a centrally located clinic and complete sessions in a lab. The at-home format of this intervention makes it uniquely easy to disseminate, and this study will fill a gap in the literature by comparing the costs and outcomes of delivering CBM both with and without an adherence promotion component. This will provide the information needed to consider whether broad dissemination and implementation of this intervention is feasible.

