##### Preliminary data evaluation

Prior to conducting data analyses, we will audit the data for completeness and quality, including missing data. We will evaluate distributions to ensure that they meet assumptions of planned analyses (see below), including the detection of outliers.

We will use a two-tailed α = .05 for the analyses of the primary outcomes. For the secondary outcomes, we will account for multiple testing by controlling the false discovery rate (10%) using the Benjamini–Hochberg procedure. All analyses will be carried out using the intent-to-treat principle by including all participants in analyses and their original arm assignments.

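### The 141 per arm expected at 12 months reflects 15% attrition, not the stated 10%, and the roughly 10% used to size the trial leaves little room for losses by the 6-month endpoint

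*Protocol article*

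**What the plan says.** All places are in the protocol article.

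- **Limitations** gives the retained sample: "Our planned sample will have approximately 141 participants in each arm at 12-month follow-up, accounting for an expected attrition rate of 10" per cent. The next sentence calls a sample of that size sufficient for the expected clinical differences.
- **Missing data** gives the attrition forecast: "Despite best efforts, we expect attrition of ~ 10% by 1 month and ~ 15% by 12 months". It plans direct maximum likelihood (ML) on all available data.
- **Power analyses** sizes the trial on Arm 3 versus Arm 2: "at an alpha level of .05, we would have 80% power to detect a 16% greater remission (odds ratio = 1.94"). The number needed for this is 148 in each of the two arms, counted at month 6. The section then says "we inflated the target sample size based on an attrition rate of ~ 10" per cent, reaching 498 in total or 166 per arm. It justifies this as follows: "This is a conservative adjustment, as the SEs from imputed data results will be less than the SEs from a complete case analysis".
- **Preliminary data evaluation** fixes the test level: "We will use a two-tailed α = .05 for the analyses of the primary outcomes".
- **Design** places the primary outcome, ADIS remission, at 6 months. **Measures** says the ADIS is given only at baseline, 6 months and 12 months.

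**The concern.** Three statements about retention do not fit together.

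1. The 141 per arm and the 10% in Limitations cannot both be right when 166 are randomised per arm.
2. The only time point that the article attaches to about 10% attrition is month 1. The contrast that set the sample size is tested at month 6, when cumulative loss can only be the same or higher.
3. The inflation is described as conservative because imputed data would give smaller standard errors. The missing-data section plans ML, not imputation, and for this outcome ML gains little from participants who are lost early.

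At stake is whether the Arm 3 versus Arm 2 comparison keeps its stated 80% power, and whether a reader can rely on the safety margin that the article claims.

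**Working it through.** **Inputs.** 166 per arm, 148 required per arm, odds ratio 1.94, 16-point difference and 80% power (Power analyses); two-sided alpha 0.05 (Preliminary data evaluation); attrition of about 10% by month 1 and about 15% by month 12 (Missing data). The base remission rate is not stated. An odds ratio of 1.94 with a 16-point difference implies about 0.34 versus 0.50, or 0.50 versus 0.66. I use 0.34 versus 0.50 as an assumption and vary the lower rate from 0.33 to 0.50.

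**1. The plan's own figures.** For two proportions with pooled variance under the null and no continuity correction:

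n = [1.96 √(2 p̄(1−p̄)) + 0.842 √(p₁(1−p₁) + p₂(1−p₂))]² / (p₂−p₁)²

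With p₁ = 0.34, p₂ = 0.50 and p̄ = 0.42, n = 148.2, or 149 when rounded up. With 0.35 and an odds ratio of exactly 1.94, n = 148. The stated 148 reproduces. The inflation also reproduces closely: 444 / 0.90 = 493.3, so 494 against the stated 498.

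**2. The retained sample.**

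- 166 × 0.90 = 149.4
- 166 × 0.85 = 141.1
- 1 − 141/166 = 15.1%

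So 141 is the 15% figure. At 10% the count would be about 8 per arm higher.

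**3. The attrition that the design can absorb.** 1 − 148/166 = 10.8%.

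**4. What remains at month 6.** No 6-month rate is given, so I take the range between the two stated rates. The middle row assumes a linear rise from month 1 to month 12: 10% + 5% × 5/11 = 12.3%.

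| Attrition at month 6 | n per arm | Power, 0.34 vs 0.50 |
|---|---|---|
| 10% | 149.4 | 80.3% |
| 10.8% | 148 | 79.9% |
| 12.3% (assumed) | 145.6 | 79.3% |
| 15% | 141 | 78.0% |

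With the odds ratio held at 1.94 and the lower rate varied from 0.33 to 0.50, power at 141 per arm runs from 77.6% to 79.0%.

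**5. The main contrast.** Arms 2 and 3 versus Arm 1 needs 187 participants in total. Even at 15% attrition, 498 × 0.85 = 423 remain, more than twice that number.

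**6. The claim of conservatism.** The planned model for remission is a logit-link hierarchical model with time and arm as predictors. Every participant has a qualifying diagnosis at baseline, so remission is the same for everyone at that point. Only the 6- and 12-month ADIS carry information on arm differences. A participant with neither adds essentially nothing to the estimated arm effect. One who misses month 6 but is seen at month 12 does contribute.

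**The case against.** The sizing itself is sound: 148 and 498 reproduce, and 166 per arm covers slightly more than 10%. The Power analyses section does not label its 10% as the 1-month rate, and no 6-month rate appears anywhere, so any shortfall at the endpoint is an inference. It is also small: under the linear assumption, power moves from 79.9% to 79.3%. All of this stands. A reader might infer that the stated sample size and 80% power are not delivered; the documents do not support that.

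A reader might also infer that 141 is plainly too few because 148 are required. But 141 is a 12-month count, and 148 is the requirement at 6 months for a deliberately reduced effect (d = 0.37). The literature review in Power analyses suggested d = 0.57 for this comparison. By the logistic conversion exp(dπ/√3), that is an odds ratio of about 2.8, for which 141 per arm give about 98% to 99% power at assumed lower remission rates of 0.20 to 0.50. If that is what *expected clinical differences* means, the sentence is defensible. The article does not say which effect is meant, so the two statements still need reconciling.

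Nor is Arm 3 versus Arm 2 the only contrast powered at 80%; the main contrast is too, and attrition does not threaten it. Finally, it would go too far to say that ML recovers nothing: participants seen at month 12 but not month 6 contribute. The article does not say how many there will be.

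**Conclusion.** The mislabelled rate is certain: 141 of 166 is 15% attrition, in line with the Missing data section and not with the 10% beside it.

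The sizing point holds in a modest form. The inflation allows for at most 10.8% loss at month 6, while the article expects about 10% by month 1 and about 15% by month 12. For Arm 3 versus Arm 2 this means about 141 to 149 per arm and power of about 78% to 80%, or about 79% under the assumed linear rise. These are complete-case figures and rest on the assumed base remission rate.

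The claim that the adjustment is conservative is not supported as written. It appeals to imputation that the missing-data section does not plan, and ML offers essentially nothing for participants with no follow-up ADIS. None of this invalidates the trial.

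**What to change.** 1. In Limitations, change 10% to 15% for the 141 per arm at 12 months.
2. In Power analyses, state the expected attrition at 6 months and the resulting n and power for Arm 3 versus Arm 2 (about 78% to 80% for rates of 15% down to 10%). Enrolment stays at 498.
3. Reconcile the statement that 141 per arm is sufficient with the 148 required, and say which effect size and time point are meant.
4. Delete the sentence that calls the adjustment conservative. Alternatively, give it substance by multiply imputing 6-month remission, with the PARS, SCARED, CGI and PHQ-9 from earlier waves as auxiliary variables. These are already collected.

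Items 1 to 3, and the deletion, are text changes, with slightly less favourable figures on the page. The imputation option costs a little more analysis work. No option needs more participants.

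### The 141 per arm at 12 months reflects 15% attrition, not the stated 10%, and the 6-month sample is inflated by the loss expected already at 1 month

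*Protocol article*

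**What the plan says.** The protocol article speaks to retention and sample size in three places.

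- **Power analyses.** For Arm 3 versus Arm 2, "we would have 80% power to detect a 16% greater remission (odds ratio = 1.94"). The number needed for this at month 6 is put at 148 in each arm, 444 in total. This contrast set the trial size. The authors then write "we inflated the target sample size based on an attrition rate of ~ 10" per cent, which gives 498, or 166 per arm. No timepoint is attached to that rate. They add: "This is a conservative adjustment, as the SEs from imputed data results will be less than the SEs from a complete case analysis".
- **Missing data.** Here "we expect attrition of ~ 10% by 1 month and ~ 15% by 12 months". No 6-month figure is given. Missing panel data are to be handled by direct maximum likelihood (ML).
- **Limitations.** "Our planned sample will have approximately 141 participants in each arm at 12-month follow-up, accounting for an expected attrition rate of 10" per cent. The next sentence begins: "A sample this size is sufficient to detect expected clinical differences".

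**The concern.** The attrition rate in Limitations does not produce the number printed beside it, and it disagrees with the rate that Missing data gives for the same timepoint.

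The allowance built into the sample size is the same 10% that Missing data expects to be lost by month 1, although the primary endpoint is at month 6. Cumulative loss cannot fall over time. On the plan's own figures, 10% is thus the lowest value that month-6 attrition would take, yet the adjustment is described as conservative.

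Readers will judge a null result for Arm 3 versus Arm 2 against these retention and power statements, so the statements should agree with one another.

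**Working it through.** **Inputs.** 166 per arm randomised, 148 per arm required, odds ratio 1.94, a 16-point difference and 80% power (Power analyses). Two-sided 5% level: "We will use a two-tailed α = .05 for the analyses of the primary outcomes" (Preliminary data evaluation). Attrition of about 10% by month 1 and about 15% by month 12 (Missing data). Primary outcome at 6 months (Design).

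**1. Does the planned sample size reproduce?** An odds ratio of 1.94 with a difference of exactly 16 points implies 34.1% versus 50.1% (or its mirror image, 49.9% versus 65.9%). The two-proportion formula without continuity correction is

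n = [z(0.975)·√(2·p̄(1−p̄)) + z(0.80)·√(p1(1−p1) + p2(1−p2))]² / (p2−p1)².

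With p1 = 0.341, p2 = 0.501 and p̄ their mean, it gives 149 per arm against the stated 148. Inflating for 10% loss, 148/0.90 = 164.4, i.e. 165 per arm, and 444/0.90 = 493.3, i.e. 494 in total. The stated 166 and 498 are consistent with this. The sample-size arithmetic itself stands.

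**2. Does 141 per arm follow from 10% attrition?**

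- 166 × 0.90 = 149.4
- 166 × 0.85 = 141.1

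It does not. The printed 141 is the 15% figure. The gap is 8 per arm, or about 24 in total.

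**3. How much attrition does 166 per arm absorb?** 1 − 148/166 = 10.8%. At exactly 10% the margin over 148 is 149.4 − 148 = 1.4 per arm.

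**4. What remains at month 6?** The plan gives no 6-month rate, so its own figures supply only the bracket from 10% to 15%. For illustration, a straight line from month 1 to month 12 gives 10 + 5 × (5/11) = 12.3%. That interpolation is an assumption of this review. Power uses the same two-proportion method, counting only those retained:

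| Attrition at month 6 | Per arm | Power, 34.1% v 50.1% | Power, 41.8% v 58.2% |
|---|---|---|---|
| 10% | 149.4 | 80.3% | 81.3% |
| 10.8% | 148.0 | 79.9% | 81.0% |
| 12.3% (interpolated) | 145.6 | 79.3% | 80.3% |
| 15% | 141.1 | 78.0% | 79.1% |

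The last column uses the control rate most favourable to an odds ratio of 1.94. Its difference of 16.4 points also rounds to 16%.

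**5. How sensitive is this to rounding?** At 145.6 per arm, control rates from 31% to 42%, all of which give a difference that rounds to 16 points, yield power from 78.1% to 80.3%. That spread of about 2 points is larger than the loss at the interpolated rate.

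**The case against.** The strongest reply is that only the mismatch between 141 and 10% is a demonstrable error. Four parts of that reply deserve an answer.

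- **No 6-month rate is stated.** At exactly 10%, 149 per arm remain and there is no shortfall. This stands. A reader might infer that the plan predicts fewer than 148, but the documents support only that this is probable: it happens at any rate above 10.8%, within a bracket of 10% to 15%.
- **The power loss lies within the rounding of the inputs.** This stands too, as step 5 shows. A precise figure such as 79.3% should not be presented as the plan's true power.
- **The sufficiency statement.** A reader might take it that calling 141 per arm sufficient contradicts the 148 required. The documents do not establish this. Power analyses separates the effect expected from the literature for Arm 3 versus Arm 2 (d = 0.57) from the smaller value chosen for powering (d = 0.37). By the usual logistic conversion, d = 0.57 is an odds ratio of exp(0.57 × π/√3) = 2.8. From a 34.1% control rate, 141 per arm then gives about 99% power. The larger contrast, Arms 2 and 3 versus Arm 1, needs only about 63 per arm.
- **Maximum likelihood recovers information.** A reader might go further and say that the ML standard error cannot be smaller than that of a complete-case analysis. That is too absolute. The ADIS is repeated at 12 months, so a youth who misses month 6 but returns at month 12 still contributes. The size of this gain is unknown, and it does not turn the lowest attrition rate in the plan's own range into a conservative allowance.

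**Conclusion.** Two points hold. First, the 10% in Limitations is wrong: 141 per arm corresponds to 15%, in agreement with Missing data. This is certain and needs no assumption. Second, the sample for the 6-month endpoint is inflated by a rate that Missing data assigns to month 1, which leaves room only up to 10.8% attrition. If month-6 attrition lies between 10% and 15%, 141 to 149 per arm are expected, probably slightly below 148.

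The consequence is small. Power for Arm 3 versus Arm 2 is about 78% to 80% over that range, at most about 2 points under the stated 80%. This rests on 34.1% versus 50.1%, a pair derived from the stated odds ratio and difference, and on counting only those retained. The label of a conservative adjustment is not supported as worded, because it appeals to imputation where the plan specifies direct ML, and because 10% is the low end of the plan's own attrition figures. The findings do not amount to a materially underpowered trial.

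**What to change.** - In Limitations, change the attrition rate beside 141 per arm from 10% to 15%.
- In Power analyses, state the sponsor's own expected attrition at 6 months, then give the resulting number per arm and power for Arm 3 versus Arm 2, together with the control remission rate assumed.
- Reword the conservative-adjustment sentence so that it refers to direct ML, and do not call a 10% allowance conservative against an expected loss of 10% by month 1 and 15% by month 12.

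The cost is a few sentences and a stated power that may be up to about 2 points lower. Enrolment, design and analysis are unchanged.
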